### Study Aims and Hypotheses

This study is designed to empirically test the controversy regarding both the value of intensive, high dosage training as well as the optimal timing for intensive VR/Robotic training in the first 2 months after stroke. We are continuing an ongoing investigation into the effects of intensive task and impairment-based training of the hemiparetic upper limb with a focus on the hand using robotically facilitated rehabilitation interventions presented in virtual environments. The primary aim of this study is to test, at 4 months post-stroke, whether adding intensive VR/Robotic motor training to a patient's standard of care rehabilitation at 5–30 days post-stroke, improves functional outcomes of the hemiparetic hand when compared to initiating the additional VR/Robotic motor training 30–60 days post-stroke; thus testing the concept of optimal timing. Other comparisons include comparing Early VR to dose-matched usual care to test the potential benefits of the high-intensity VR/Robotic intervention. Comparing dose-matched usual care (10 additional hours of standard therapy) to usual care (no additional therapy) will inform about the benefits of increased dosing (Table 1). See controversies elucidated in recent literature (12, 30). We hypothesize that the outcomes will favor the early, high dosage VR/Robotic hand training group when compared to the delayed VR/Robotic training group and dose matched usual care group. The secondary aims will systematically investigate the mechanisms underlying the changes resulting from early timing of training and increased dosing, specifically changes in kinematics, kinetics, patterns of cortical somatotopic reorganization, and brain connectivity. We further hypothesize that the early, high dosage VR/Robotic hand training group will show a larger relative contribution of restored kinematic motor patterns to the overall improvement in motor function and these functional gains will be associated with the expansion of ipsilesional hand cortical somatotopy.

**Table 1 T1:** Comparison groups.

**Group comparisons**	**Intervention period^**+**^**	**Test**
EVR vs. DVR^*^	5–30 vs. 30–60 days	Timing of a VR/robotic intervention
EVR vs. DMUC^**^	5–30 days	VR/Robotic vs. conventional intervention
DMUC vs. UC^***^	5–30 days	Dosing of an intervention

* Early Virtual Reality vs. Delayed Virtual Reality,

** Dose Matched Usual Care,

*** *Usual Care; ^+^Time Post-Stroke*.

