### Randomization and Recruitment

An independent statistician will generate the randomization sequence prior to initiation of the study. Physicians and therapists will identify potential subjects. The study coordinator will contact the patients as soon as they are medically stable, inform them about the study, screen them for inclusion and exclusion criteria and enroll them. The subjects will be stratified on two dimensions, impairment level and presence or absence of Motor Evoked Potentials (MEPs). Prior to randomization, potential subjects will be assessed using the Upper Extremity Fugl-Meyer Assessment (FM) (33) to establish motor impairment level, and Transcranial Magnetic Stimulation (TMS) for the presence or absence of MEPs in the lesioned hemisphere. These scores will be used to stratify subjects into four subgroups; (1) Severe, FM score 10–19, MEP+, (2) Severe, FM score 10–19, MEP–, (3) Moderate, FM score 20–49, MEP+, (4) Moderate, FM score 20–49, MEP-. If a subject is not eligible for TMS, he/she will be assigned to either group 2 (if severe) or group 3 (if moderate). This is based on the Stinear et al. (34) study in which study subjects with moderate impairment all had MEPs (34). Stratified block randomization will then be used to achieve a balanced assignment (35). For each of the four subgroups, every 4 subjects are one block. In each block, there is one subject for each type of treatment. One hundred twenty subjects will be assigned sequentially to four types of treatment groups (30 per group): (a) state-of-art usual care only (UC), (b) usual care plus an additional 10 h of usual care (dose-matched usual care, DMUC; initiated 5–30 days post-stroke), (c) usual care plus an additional 10 h of intensive therapy focusing on the hand using robotically facilitated rehabilitation interventions presented in virtual environments initiated **early** (5–30 days post-stroke) (EVR), and (d) usual care plus an additional 10 h of intensive therapy focusing on the hand using robotically facilitated rehabilitation interventions presented in virtual environments initiated later (30–60 days post stroke) (DVR) (see Figure 1).

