### Sample Size

For Aim 1, the planned primary analysis method is a mixed effect model. The primary outcome measure is the change in ARAT score from baseline evaluated at 4 months post-stroke. The estimated effect size for the interaction term is 0.42 (Cohen's f), and the estimated within-subject correlation is 0.7. For testing the hypothesis of Treatment Group (EVR, DVR, UC, DMUC) ^*^Test Time (Baseline, 4 M post-stroke, 6 M post-stroke) effect, and assuming compound symmetry correlation for within-subject measurements, for significance level 0.05, a total of 84 patients (21 for each group) are needed to detect the overall Treatment Group ^*^ Test Time interaction effect. But for the main planned contrasts, Treatment Group (EVR, DVR) ^*^ Test Time (Baseline, 4 M post-stroke) and Treatment Group (UC, DMUC) ^*^ Test Time (Baseline, 4 M post-stroke), a total of 96 patients (24 for each group) are required to detect the effect size of 0.42 between EVR and DVR or between UC and DMUC over time. Since detecting these contrasts is the main goal of the study, at least 96 subjects, 24 subjects per group, are required. After taking into account subject attrition, our total sample size will be equal to 120. We plan to run an interim analysis and update the sample size when we have recruited 50% of subjects.

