### Statistical Analysis

The primary aim of the study is to test, at 4 months post-stroke, whether intensive VR/Robotic motor training initiated 5–30 days post-stroke, improves functional outcomes of the hemiparetic arm and hand when compared to VR/Robotic motor training initiated on 30–60 days post-stroke. Other comparsions include evaluating the type of training (EVR vs. DMUC) and dosing (DMUC vs. UC) initiated within 5–30 days post-stroke. The secondary aims will systematically investigate the mechanisms underlying the changes resulting from the early timing of training and increased dosing. Aim 2 will quantify the recovery and compensation profiles by examining the changes in kinematics and kinetics of the hand and arm associated with this training and Aim 3 will quantify patterns of cortical somatotopic reorganization and will investigate the relationship among these patterns of reorganization and the clinical and biomechanical outcomes.

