We will use the robust mixed effect model approach to analyze the data. We demonstrated in the past that this analytic approach is robust to detect treatment effects, even with relatively small groups of patients in whom within-group variance occurs with respect to stroke characteristics (56). Test Time (Pre, Post, 1-month post-treatment, 4 months post-stroke, 6 months post-stroke) and Treatment Group (EVR, DVR, DMUC, UC) will be treated as fixed effects in the mixed models. The interaction term between Test Time and Treatment Group will be included. Baseline measurements will be added as a covariate into mixed models for outcome variables. Random intercept will be used to model subject-level variation. Covariance pattern and model selection will be implemented with likelihood-based tests. Contrasts to compare group means will be applied to obtain comparisons between time, and between treatments, with multiplicity adjustment considered. We have an a priori interest in specific Test Time by Treatment Group interaction effects for the EVR-DVR, for the DMUC-UC, and for the EVR-DMUC comparisons. The particular differences we are interested in are Pre vs. Post and Pre vs. second (4 months post stroke) retention assessments. In the case of balanced data and equal variances, we will use the Tukey procedure to test for significant interaction effects, otherwise, Bonferroni correction will be used. In our design, the timing comparison is the difference between EVR and DVR. The dosage comparison is the difference between UC (usual care) and the DMUC (usual care plus 10 additional hours). In addition, we will be able to compare the type of training effect, VR vs. dose-matched usual care (EVR vs. DMUC), where both types of training are delivered in the same time period.

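### Sample Size makes timing (EVR-DVR) and dosing (DMUC-UC) a joint main goal, while the aims name EVR-DVR alone as primary; 24 per group reaches 80% power only for a contrast tested at unadjusted 0.05

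*Protocol article*

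**What the plan says.** **Study Aims and Hypotheses.** The primary aim is EVR against DVR at 4 months post-stroke. EVR-DMUC and DMUC-UC are introduced afterwards as other comparisons. The hypothesis on functional outcome is that EVR does better "when compared to the delayed VR/Robotic training group and dose matched usual care group". No direction is hypothesised for DMUC against UC, which is said only to be informative about dosing.

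**Statistical Analysis, opening paragraph.** The primary aim is repeated as EVR-DVR alone: whether early training "improves functional outcomes of the hemiparetic arm and hand when compared to VR/Robotic motor training initiated on 30–60 days post-stroke". Type of training (EVR-DMUC) and dosing (DMUC-UC) again come second.

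**Statistical Analysis, mixed-model paragraph.** A priori interest is declared "for the EVR-DVR, for the DMUC-UC, and for the EVR-DMUC comparisons". Tukey is planned for balanced data with equal variances and Bonferroni otherwise. The paragraph then presents EVR-DVR and DMUC-UC as the design's timing and dosage comparisons and EVR-DMUC as an additional possibility.

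**Sample Size.** The main planned contrasts are EVR-DVR and UC-DMUC; 96 patients "are required to detect the effect size of 0.42 between EVR and DVR or between UC and DMUC over time". The section concludes: "Since detecting these contrasts is the main goal of the study, at least 96 subjects, 24 subjects per group, are required". EVR-DMUC is not mentioned. The section also plans an interim analysis and a sample-size update at 50% recruitment.

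**The concern.** Sample Size cannot be reconciled with the primary aim as it is stated twice elsewhere. It raises a contrast with no directional hypothesis (DMUC-UC) to a joint main goal, and it leaves out one of the two contrasts that do carry a hypothesis (EVR-DMUC).

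Three things depend on this:

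- **The main conclusion.** If EVR-DVR is null and DMUC-UC is positive, a report that follows Sample Size and one that follows the aims would describe the trial differently.
- **The interim update.** The text does not settle which contrast's data would drive the revised sample size.
- **The meaning of 24 per group.** That figure rests on each contrast having the full 0.05. If two or three contrasts share the error rate under the planned adjustment, it no longer delivers the same power.

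**Working it through.** **Inputs from the protocol article**

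- Effect size and correlation (Sample Size): "The estimated effect size for the interaction term is 0.42 (Cohen's f), and the estimated within-subject correlation is 0.7".
- Significance level and overall test (Sample Size): "for significance level 0.05, a total of 84 patients (21 for each group) are needed to detect the overall Treatment Group"-by-time interaction.
- Allocation (Randomization and Recruitment): "One hundred twenty subjects will be assigned sequentially to four types of treatment groups (30 per group").
- Power is not stated. I assume 80%, which reproduces both stated totals; 85% and 90% do not.
- The attrition rate is not stated. Going from 96 to 120 implies 20%, since 96 / (1 − 0.20) = 120.

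**Step 1. Reproduce the plan's figures.** Use a noncentral F test of the interaction with λ = f² × N, df1 = (k − 1)(m − 1) and df2 = (N − k)(m − 1), for k groups and m times. Take f as the effect on the interaction itself, so that the correlation of 0.7 is not applied a second time.

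- Overall, k = 4, m = 3, N = 84: λ = 0.1764 × 84 = 14.82, df = 6 and 160, power 82.0%. The smallest balanced N reaching 80% is 84, as stated.
- One pair, k = 2, m = 2, N = 48: λ = 0.1764 × 48 = 8.47, df = 1 and 46, power 81.3%. The smallest N reaching 80% is 48, that is 24 per group and 96 over four groups, as stated.

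The pair calculation equals a two-sided two-sample t test with d = 2f = 0.84. Applying the correlation again would give 12 in total and 10 per pair, which does not match. So the 24 per group is a figure for one contrast at unadjusted 0.05.

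**Step 2. Power per contrast at 24 per group under an adjustment.** Same t test, d = 0.84:

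| Contrasts sharing 0.05 (Bonferroni) | Level per contrast | Power, 24 per group | n per group for 80% | Completers | Enrolled, 20% attrition |
|---|---|---|---|---|---|
| 1 | 0.05 | 81% | 24 | 96 | 120 |
| 2 | 0.025 | 72% | 29 | 116 | 145 |
| 3 | 0.0167 | 66% | 32 | 128 | 160 |

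Pooling the variance over four groups (92 df) changes the three powers only to 82%, 74% and 68%. Tukey over all four groups (critical value 2.617, 92 df) gives 62%.

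If nobody dropped out and all 30 per group were analysed, the t test would give 89%, 83% and 78% for one, two and three contrasts.

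**Step 3. Status of each contrast, side by side**

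| Contrast | Primary aim (stated twice) | Hypothesised direction | Sample Size |
|---|---|---|---|
| EVR-DVR | Primary | Yes | Main goal |
| EVR-DMUC | Other comparison | Yes | Absent |
| DMUC-UC | Other comparison | None stated | Main goal |

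Only EVR-DVR has the same rank throughout.

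**The case against.** **Multiplicity is already addressed.** A reader might infer that two main-goal contrasts at 0.05 each mean a false-claim rate of 1 − 0.95² = 9.75%. The article does not support that. Statistical Analysis plans Tukey or Bonferroni, the 0.05 in Sample Size is a sizing input, and nowhere is it said that either contrast alone makes the trial a success. The 9.75% would apply only to unadjusted tests combined with an either-contrast-wins rule. This objection stands in full, and it moves the cost from error rate to power.

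**Dosing is a declared purpose.** The Abstract and Discussion present the study as testing both dosing and timing, so pairing the two contrasts is not arbitrary. The mixed-model paragraph leans the same way, treating EVR-DMUC as an addition; it would be wrong to say that it gives the three contrasts equal standing. This stands as an explanation of how Sample Size came to be worded. It does not remove the conflict with a primary aim stated twice as EVR-DVR alone. It does mean that the investigators could instead declare two main contrasts, but they would then need to size at the adjusted level.

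**Omitting EVR-DMUC does not change N.** With equal allocation, 24 per group serves any pair of arms at f = 0.42 and unadjusted 0.05. That is correct, but only under those two conditions. The article assumes no effect size for a comparison against an active dose-matched arm, and the planned adjustment removes the second condition.

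**Conclusion.** The contradiction is real and lies in the current text: Sample Size has two main contrasts, while the aims and the analysis section have one primary aim. It leaves unsettled which contrast decides the main conclusion and which drives the 50% update.

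The stated 96 is arithmetically sound for a single contrast at 0.05 (81% power). If Bonferroni applies over the two main contrasts, power is about 72% each; over all three a priori contrasts it is about 66%. These figures assume f = 0.42 for every contrast, an 80% target inferred from the stated totals, and 24 completers per group.

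A reader might go further and conclude that type I error is inflated, or that a positive dosing result is licensed as overall success. Neither follows, because an adjustment is planned and Sample Size defines no success rule. What stands is a consistency fault that should be corrected, with a consequence for power.

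**What to change.** **In Sample Size:**

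- Name EVR-DVR at 4 months, tested at 0.05, as the one contrast that sets N and the interim update, in line with the two statements of the primary aim.
- Delete the sentence that makes the plural contrasts the main goal.
- List EVR-DMUC and DMUC-UC as secondary contrasts under the adjustment in Statistical Analysis. State their adjusted power: about 72% each with Bonferroni over the two at 24 per group, if f = 0.42 holds. Do not say that 24 per group covers them.

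**In Statistical Analysis:** state that the Tukey or Bonferroni adjustment for the 4-month ARAT applies to the secondary contrasts and not to EVR-DVR. If EVR-DVR were adjusted with the other two, its power would fall to about 66%.

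**Cost:** wording only. N stays at 96 completers and 120 enrolled. The downside is that the dosing contrast is reported as secondary. If the investigators prefer to keep it as a joint main contrast, Bonferroni over two needs 29 per group, which is 116 completers or 145 enrolled at the implied 20% attrition. The article reports only seven subjects through their 6-month tests, so the change should be made before the interim analysis.

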### Statistical Analysis

The primary aim of the study is to test, at 4 months post-stroke, whether intensive VR/Robotic motor training initiated 5–30 days post-stroke, improves functional outcomes of the hemiparetic arm and hand when compared to VR/Robotic motor training initiated on 30–60 days post-stroke. Other comparsions include evaluating the type of training (EVR vs. DMUC) and dosing (DMUC vs. UC) initiated within 5–30 days post-stroke. The secondary aims will systematically investigate the mechanisms underlying the changes resulting from the early timing of training and increased dosing. Aim 2 will quantify the recovery and compensation profiles by examining the changes in kinematics and kinetics of the hand and arm associated with this training and Aim 3 will quantify patterns of cortical somatotopic reorganization and will investigate the relationship among these patterns of reorganization and the clinical and biomechanical outcomes.

We will use the robust mixed effect model approach to analyze the data. We demonstrated in the past that this analytic approach is robust to detect treatment effects, even with relatively small groups of patients in whom within-group variance occurs with respect to stroke characteristics (56). Test Time (Pre, Post, 1-month post-treatment, 4 months post-stroke, 6 months post-stroke) and Treatment Group (EVR, DVR, DMUC, UC) will be treated as fixed effects in the mixed models. The interaction term between Test Time and Treatment Group will be included. Baseline measurements will be added as a covariate into mixed models for outcome variables. Random intercept will be used to model subject-level variation. Covariance pattern and model selection will be implemented with likelihood-based tests. Contrasts to compare group means will be applied to obtain comparisons between time, and between treatments, with multiplicity adjustment considered. We have an a priori interest in specific Test Time by Treatment Group interaction effects for the EVR-DVR, for the DMUC-UC, and for the EVR-DMUC comparisons. The particular differences we are interested in are Pre vs. Post and Pre vs. second (4 months post stroke) retention assessments. In the case of balanced data and equal variances, we will use the Tukey procedure to test for significant interaction effects, otherwise, Bonferroni correction will be used. In our design, the timing comparison is the difference between EVR and DVR. The dosage comparison is the difference between UC (usual care) and the DMUC (usual care plus 10 additional hours). In addition, we will be able to compare the type of training effect, VR vs. dose-matched usual care (EVR vs. DMUC), where both types of training are delivered in the same time period.

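### Baseline enters the mixed model both as the Pre response and as a covariate, so the covariate adds nothing to the named Pre-to-4-month contrast and precision is given up

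*Protocol article*

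**What the plan says.** All of the following is in the protocol article.

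- **Response and fixed effects** (Statistical Analysis): "Test Time (Pre, Post, 1-month post-treatment, 4 months post-stroke, 6 months post-stroke) and Treatment Group (EVR, DVR, DMUC, UC) will be treated as fixed effects". The next sentence adds "The interaction term between Test Time and Treatment Group will be included".
- **Covariate, same model:** "Baseline measurements will be added as a covariate into mixed models for outcome variables". No baseline-by-time term is given, and nothing takes Pre out of the response.
- **Subject effect:** "Random intercept will be used to model subject-level variation". The covariance pattern is then to be chosen by likelihood-based tests.
- **Contrasts of interest:** "The particular differences we are interested in are Pre vs. Post and Pre vs. second (4 months post stroke) retention assessments", each compared between groups (EVR-DVR, DMUC-UC, EVR-DMUC).
- **Endpoint and planning** (Sample Size): "The primary outcome measure is the change in ARAT score from baseline evaluated at 4 months post-stroke". The planning values are stated as "The estimated effect size for the interaction term is 0.42 (Cohen's f), and the estimated within-subject correlation is 0.7", with compound symmetry and a significance level of 0.05. The result is 24 per group for the two-group by (Baseline, 4 months) contrasts.
- **Missing data** (Management of Missing Data and Dropouts): listwise exclusion, with multiple imputation as a sensitivity analysis.
- **Two Pre tests in DVR** (Measures; footnote to Table 2): DVR is tested once after enrollment in hospital and again just before its delayed intervention.

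**The concern.** Sample Size calls the first Test Time level Baseline where Statistical Analysis calls it Pre, so the covariate and the Pre response are the same occasion. The model then explains the Pre row partly by itself, and one common slope is imposed on every visit.

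A reader of the covariate sentence would expect the efficiency of a baseline-adjusted analysis, in which the data estimate the weight given to baseline. The named contrasts do not deliver that. What is at stake is the precision of the main comparison in a trial that expects only 25–30 patients a year (Current Results), and whether the planned covariance selection can be carried out as described.

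**Working it through.** **1. The plan's own figure.** Power is not stated; I assume 80%.
- Two-group contrast, noncentral F with λ = f²N. With N = 48, λ = 0.42² × 48 = 8.47 on 1 and 46 df, and power is 81.3%. With N = 46 it is 79.6%. So 24 per group reproduces.
- Overall 4 × 3 interaction, same λ, df 6 and 2(N − 4). N = 84 gives 82.1% and N = 80 gives 79.7%, so 84 reproduces too.
- The contrast calculation equals a two-sample test on change scores with d = 2f = 0.84 change-SDs. It assumes no gain from a baseline covariate.

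**2. Why the covariate cancels.** Let x be a patient's baseline and b its common slope. With complete data and a full Group × Time mean structure, the fitted effect for group g at visit t is ȳ(g,t) − b·x̄(g). For EVR and DVR:

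[ȳ(E,4M) − b·x̄(E)] − [ȳ(E,Pre) − b·x̄(E)] − {the same for D} = difference in mean change.

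The term in b drops out whatever its value. It also drops out if DVR's covariate is taken from its other Pre test.

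**3. Numerical check.** I used 60 simulated complete trials (4 groups × 24, 5 visits, compound symmetry 0.7, unit variance), fitted by REML with a random intercept.

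| Quantity | Result |
|---|---|
| Largest change in the Pre-to-4-month contrast when the covariate is added | 4 × 10⁻¹⁴ |
| Mean SE without / with the covariate | 0.2211 / 0.2211 (largest difference 2 × 10⁻⁶) |
| Mean SE, ANCOVA at 4 months | 0.2036 |
| Mean SE, post-baseline visits only, baseline covariate | 0.2049 (0.2054 with baseline × visit) |
| Variance ratio, ANCOVA / change score | 0.853 |

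Theory gives √(0.60 × 2/24) = 0.2236 for change and √(0.51 × 2/24) = 0.2062 for ANCOVA.

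**4. Size of the gain with equal variances.** Ratio = (1 − ρ²)/[2(1 − ρ)] = (1 + ρ)/2. Change-score power is 81.3% throughout, because d is fixed in change-SDs. ANCOVA power uses λ = n·d²/(2 × ratio) on 1 and 2n − 3 df; at ρ = 0.7, λ = 24 × 0.7056/1.70 = 9.96.

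| ρ | Variance ratio | ANCOVA power at 24 per group | n per group for 80% |
|---|---|---|---|
| 0.5 | 0.75 | 90.8% | 18 |
| 0.7 | 0.85 | 87.0% | 20 |
| 0.8 | 0.90 | 85.1% | 22 |
| 0.9 | 0.95 | 83.2% | 23 |

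**5. Unequal variances.** With k = SD(4M)/SD(baseline), the ratio is k²(1 − ρ²)/(1 + k² − 2ρk). At ρ = 0.7:
- k = 1: 0.85
- k = 1.2: 1.44 × 0.51/0.76 = 0.97
- k = 1.43 (where ρk = 1): 1.00
- k < 1: a larger gain than at k = 1

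The article gives no ARAT SDs, so k is unknown.

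**6. Covariance selection.** Suppose a candidate structure gives Pre its own variance, as an unstructured matrix does. As b approaches 1, the Pre residual approaches 0 for every patient and the likelihood has no upper bound. On one simulated data set (96 patients, 5 visits, correlation 0.7) the profile log-likelihood was −442 at b = 0, 0.5 at 0.99, 222 at 0.999 and 443 at 0.9999. Each tenfold fall in 1 − b adds 96 × ln 10 = 221. Such a candidate either fails to converge or wins for no meaningful reason. This needs the covariate and the Pre row to be the same measurement. It does not affect structures with one variance for all visits.

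**The case against.** **Other readings of the text.** Sample Size defines the outcome as change, and Statistical Analysis also mentions contrasts of group means. If change were the response, or if the contrast were groups at 4 months alone, the covariate would do real work. The first reading does not fit the stated Test Time levels, since change at Pre is zero for everyone. The second does not fit the contrasts named as of a priori interest, which all start from Pre. An analysis plan not shown may settle the coding, but the article states a specific model and that model has this property.

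**Stronger inferences that do not hold.**
- *The trial is underpowered or the estimate biased.* It is neither for this reason. The contrast is a valid difference in change, and 24 per group reproduces as a change-score calculation.
- *The analysis is unadjusted for baseline.* A change score adjusts with slope 1. The fair criticism is that this slope may not be the best one, so some regression-to-the-mean effect of chance imbalance can remain. Stratifying by Fugl-Meyer band and MEP status in blocks of four (Randomization and Recruitment) limits such imbalance in motor severity.
- *Type I error is inflated because a random intercept is used.* That would depend on an assumed decay of correlation, and the plan goes on to select the covariance pattern. It is also a separate matter: under the random intercept the SE is the same with and without the covariate.

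**What stands of the objection.** The size of the gain is conditional and may be small. The cancellation is exact only for complete data, which listwise exclusion provides; with incomplete data the covariate could move the contrast slightly. The SE identity was checked for the random-intercept model with five visits.

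**Conclusion.** The point holds as one of specification and efficiency. As written, the baseline covariate has no effect on the contrast the trial is built around. The forgone gain is about 15% of variance, or roughly 6 points of power at 24 per group, if the correlation is 0.7 and the baseline and 4-month variances are equal. With equal variances it ranges from 25% at ρ = 0.5 to 5% at ρ = 0.9. It is about 3% at ρ = 0.7 if the 4-month SD is 1.2 times the baseline SD. The 80% power target behind these comparisons is assumed.

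Separately from efficiency, the likelihood-based covariance selection cannot work for structures that give Pre its own variance while Pre is also the covariate.

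**What to change.** Use one of two models, not both:

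- **(a)** Take Pre out of the response. Model Post, 1 month, 4 months and 6 months with Group, Visit, Group × Visit, baseline and baseline × Visit. The primary contrast is the adjusted group difference at 4 months.
- **(b)** Keep Pre in the response, constrain its mean to be common across arms, and drop the covariate.

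Either choice removes the degeneracy, so an unstructured matrix can be a candidate.

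Define baseline in every arm as the first assessment after enrollment. For DVR this is the in-hospital Pre test; the later pre-intervention test is measured after randomization and should not serve as the covariate. Reword the Pre-based contrasts in Sample Size and Statistical Analysis to match.

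The cost is wording and a few extra model parameters. No new data are needed, and the planned sample size need not change. It is best settled before the interim analysis and sample-size update at 50% recruitment.
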